### Randomisation

Participants will be randomised by a member of the local research team using a computer-based tool (REDCap), stratified by study site and operation type (THR/TKR), with full allocation concealment. Randomisation will be conducted as soon as possible after the research team receive a completed baseline questionnaire. Participants will be informed of their treatment allocation by letter, followed by a telephone call for participants randomised to the intervention group to discuss arrangements for the intervention. Blinding of study participants will not be possible due to the nature of this intervention. After participants have been randomised, a letter will be sent to their GP to inform them of their participation in the Joint PREP study and their treatment allocation.

### Usual care

All participants in the study will receive their usual care. Participants randomised to the usual care group will not receive any additional advice or treatment to that provided routinely by their healthcare team. Usual care can vary between NHS trusts but may involve education classes, physiotherapy, group exercise, occupational therapy, and surgeon review before and after joint replacement. We will capture what constitutes usual care at each study site and will record details of any other preoperative exercise or nutrition programme(s) the participant is following as part of their usual care.

### Intervention

Participants randomised to the intervention arm will undertake 12 weeks of a preoperative exercise and protein supplementation intervention. The intervention was designed as a personalised and home-based programme with regular contact and support to maximise success [23]. An intervention duration of 12 weeks was informed by previous research that at least this duration of exercise is required to have benefits relevant to frailty [18]. Reporting of the intervention follows guidance from the template for intervention description and replication (TIDieR) [24], and a TIDieR checklist is provided in Additional file 2.

#### Exercise

Participants will have an initial 1:1 appointment with a trained physiotherapist (either in person at the hospital or virtually via a secure video platform) to introduce the intervention and develop a 12-week individualised home-based exercise programme. A risk assessment will be carried out and will inform adaptation of exercises and progression schedule to ensure they are tailored to individual physical capabilities and to minimise risk. Appropriate progressions (difficulty and number of repetitions) will be agreed, and participants will be supported with telephone calls every 2 weeks to gradually increase their levels of moderate physical activity throughout the intervention period. The exercises and resources are based on the NEMEX-TJR programme (https://nemex.trekeducation.org) and have been adapted for home use with permission from the Translating Research Evidence and Knowledge programme at La Trobe University, Australia (https://trekeducation.org). The exercises include a warmup, pelvic lifts, sit-ups, lunges, sideway lunges, knee flexion and extension, hip abduction and adduction, chair stands, step-ups, and a cool down. Participants will be provided with two booklets to assist them with completing the exercises. One booklet will have instructions and illustrations for each of the exercises, and the other will have more general information about maintaining exercise, goal setting, pacing, and how best to deal with setbacks. Participants will also be offered the option of signing up to an online platform to support the home-exercise programme. All participants will be issued with Therabands (of varying resistance) for the knee and hip exercises, and where appropriate, participants will be issued with an exercise step and/or gym ball.

#### Protein

Participants will be asked to consume 20 g of additional protein in the form of one pot of jelly (118 ml) each day for 12 weeks prior to their surgery (ProSource jelly from NUTRINOVO, Wiltshire, UK). Participants who do not eat gelatine will be offered an alternative product vanilla-flavoured whey or fava bean protein powder or chocolate pea protein powder (Pulsin, Gloucester, UK) that does not contain gelatine. Participants will be asked to consume the protein within 3 h after exercise as muscle protein synthesis peaks during this time [25]. They will also be advised to consume the protein between meals to minimise any effect on appetite. Participants will be provided with instructions for eating the jelly pots or making up and drinking the powder shakes. Batches of jelly pots/protein powder will be posted to participants at regular intervals to avoid the need to store large quantities in their home. Provision of protein supplements will cease after 12 weeks; however, participants will have the option to continuing to purchase their own protein supplements after this time period.

#### Telephone follow-up calls

Participants will be telephoned by a physiotherapist six times over the 12-week intervention period, at approximately 1, 2, 4, 6, 8, and 10 weeks. The purpose of the telephone calls will be to check that participants are coping with the exercises and the additional protein, review and consider appropriate progression of exercises, and to address any problems or concerns participants may have. In the final telephone call, continuation of the home exercise programme until the time of surgery (if relevant) will be discussed.

#### Intervention training

Physiotherapists delivering the intervention will have attended a half-day training session from the study team nutritionist and physiotherapist and will have been provided with an intervention training manual. They will have experience of working clinically with patients undergoing joint replacement.

#### Assessment of contamination

An estimate of protein adequacy in usual diet and usual physical activity data will be collected from all participants via study questionnaires to explore if participation in the study has influenced the behaviour of participants randomised to the usual care group. Participants in the usual care group will also be asked if they made any changes to their diet or physical activity over the 12-week intervention period.

### Questionnaires and data collection

All participants will be asked to complete questionnaires at baseline (after recruitment and prior to randomisation) and 12 weeks after randomisation. Questionnaires will be administered on paper or online, depending on participant preference. Nonresponders will be followed up with a reminder questionnaire and then a telephone call from the local research team to offer the option of completing the outcome measures over the telephone.

A schedule of assessment is provided in Table 1. Pain and function will be assessed using the Western Ontario and McMaster Universities Osteoarthritis Index (WOMAC) [26]. Health-related quality of life will be measured using the EQ-5D-5L [27] and capabilities with the ICECAP-O [28]. Other measures include the Groningen Frailty Indicator, Clinical Frailty Scale, Global Physical Activity Questionnaire [29], Exercise Self-Efficacy and Beliefs Questionnaire [30], and Protein Screener 55 + [31]. Participants will be asked to self-report their height and weight to allow BMI to be calculated. Participants in the usual care group will be asked about any changes to usual diet or usual exercise/physical activity in the past 12 weeks and, if so, what these changes were. Participants in the intervention group will be asked questions on the acceptability of the intervention.

The Clinical Frailty Scale will be completed by a healthcare professional when the patient attends the hospital for their routine preoperative assessment appointment so that self-reported and clinician-assessed versions of the Clinical Frailty Scale can be compared. Data will be extracted from participants’ medical records on preoperative comorbidities, indication for surgery, surgery details, length of hospital stay, discharge destination, preadmission residence, post-operative mobilisation, and post-operative complications up to 30 days after surgery (if surgery takes place within the study timeframe).

### Outcome assessment and progression criteria

#### Primary feasibility outcomes

The primary outcome is to determine the feasibility of a definitive RCT. This will involve evaluation of the key parameters of uncertainty for a RCT which are eligibility and recruitment rates, adherence to the intervention, and acceptability of the trial and the intervention. Eligibility and recruitment will be assessed by collecting detailed screening and recruitment records to allow review of the number of eligible, approached, and consented patients, alongside information on reasons for non-eligibility and nonparticipation. To assess adherence to the intervention, participants will be provided with a log form and asked to keep a daily record of whether they eat their protein and complete their exercises. Further details about reasons for non-adherence will be recorded on a proforma during the intervention telephone calls. Participants will be considered to have adhered to the intervention if they consumed the protein on at least 4 days per week for at least 10 weeks and/or completed the exercises at least 3 days per week for at least 10 weeks (or 80% of intervention duration if the time available for the intervention is shorter than 12 weeks, e.g. if the participant is offered an operation date earlier than expected). Acceptability of the trial and intervention will be evaluated through qualitative interviews, questions in the study questionnaires, retention rates, and reasons for withdrawal.

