**Methods:**

The Joint PRehabilitation with Exercise and Protein (Joint PREP) study is a feasibility study for a multicentre, two-arm, parallel group, pragmatic, RCT to evaluate the clinical and cost-effectiveness of prehabilitation for frail patients undergoing total hip or knee replacement. Sixty people who are ≥ 65 years of age, frail according to the self-reported Groningen Frailty Indicator, and scheduled to undergo total hip or knee replacement at 2–3 hospitals in England and Wales will be recruited and randomly allocated on a 1:1 ratio to the intervention or usual care group. The usual care group will receive the standard care at their hospital. The intervention group will be given a daily protein supplement and will be asked to follow a home-based, tailored daily exercise programme for 12 weeks before their operation, in addition to usual care. Participants will be supported through six follow-up calls from a physiotherapist during the 12-week intervention period. Study questionnaires will be administered at baseline and 12 weeks after randomisation. Embedded qualitative research with patients will explore their experiences of participating, reasons for nonparticipation, and/or reasons for withdrawal or treatment discontinuation. Primary feasibility outcomes will be eligibility and recruitment rates, adherence to the intervention, and acceptability of the trial and the intervention.

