### Aims and objectives

The aim of the study is to estimate the extent to which a full-scale RCT of the clinical and cost-effectiveness of preoperative protein supplementation and structured exercise intervention in frail individuals waiting for a THR or TKR is feasible. Specific objectives are to estimate eligibility, recruitment and retention rates, adherence to and acceptability of the trial, data completion rates, and efficacy potential.

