Protein supplementation is an important component of prehabilitation. Large observational studies have shown inverse associations between protein intakes and risk of frailty [40, 41]. It has been suggested that exercise sensitises muscles to dietary protein, resulting in more of the available amino acids being synthesised into skeletal muscle protein [42]. A systematic review of studies in older people showed the combination of protein and muscle-strengthening exercise was associated with improvements in lean mass, leg strength, and walking capability [43]. International guidelines also suggest the combination of exercise and protein may improve frailty, gait speed, grip strength, and physical performance in older adults with frailty/prefrailty [44], and the European Society for Clinical Nutrition and Metabolism recommends that healthy older people should consume at least 1.0–1.2 g protein/kg body weight/day and take part in daily exercise [45].

In conclusion, this feasibility study is being conducted in preparation for a RCT to generate high-quality evidence on a prehabilitation intervention which aims to improve outcomes for frail patients undergoing THR or TKR. Research using linked NHS primary and secondary care electronic health records demonstrated that most patients with frailty do experience improvement in symptoms with joint replacement, although frailty is associated with worse pain and function after surgery [12]. Research is needed to understand how to optimise the amount of benefit that frail patients experience when undergoing TKR or THR.

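### Adherence is met by the protein target or the exercise target alone, so the progression criterion does not show whether the combined intervention was delivered

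*Protocol article*

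**What the plan says.** The protocol article describes one intervention with two parts. Under Intervention, participants in that arm "will undertake 12 weeks of a preoperative exercise and protein supplementation intervention". The abstract says they "will be given a daily protein supplement and will be asked to follow a home-based, tailored daily exercise programme for 12 weeks before their operation". Aims and objectives poses the feasibility question for a "preoperative protein supplementation and structured exercise intervention". The Discussion gives a reason for pairing the parts, offered as a suggestion: "exercise sensitises muscles to dietary protein, resulting in more of the available amino acids being synthesised into skeletal muscle protein".

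The scoring rule is under Primary feasibility outcomes. It sets a protein target of 4 or more days weekly and links it to the exercise target as follows: "for at least 10 weeks and/or completed the exercises at least 3 days per week for at least 10 weeks". If the intervention period is cut short, 80% of its duration replaces the 10 weeks. A daily log records both components.

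Under Progression criteria for a full-scale RCT, adherence is one of three deciding rates. Its bar is > 37%, derived from an expected 50% in 60 participants. All three rates above their bars means feasible, one or two failures means consider modification, and three failures means not feasible. No section requires both components, sets a bar for each, or explains why one suffices.

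**The concern.** Read literally, the connector is an inclusive or, because participants who meet both targets already belong to the group who meet at least one. Someone who takes the supplement and never exercises is scored as having adhered to the intervention, and so is someone who exercises and never takes the supplement. The rate answers whether people did at least one part. The full RCT needs to know whether people will do the package.

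Adherence is both a primary feasibility outcome and a progression element. The amber category exists to prompt changes, and the article's own examples include different protein products or exercises. If one component is failing and the other carries the rate, that prompt is lost. This is a stated scoring rule, not a detail left to a fuller document.

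**Working it through.** **Inputs from the protocol article.** Total sample 60, allocated 1:1, so about 30 in the intervention arm (abstract, Methods). Adherence bar > 37%, from 50% and n = 60 (Progression criteria). The article gives no component rates and no overlap; those used below are assumptions.

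**1. Reproduce the bar.** Normal-approximation lower limit: p − 1.96 × √(p(1 − p)/n).
- Adherence: 0.50 − 1.96 × √(0.25/60) = 0.50 − 0.1265 = 0.373, the stated 37%.
- The same formula gives 0.236 for recruitment (30%, n = 200) and 0.699 for retention (80%, n = 60), consistent with the stated 23% and 70%.

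**2. Pass mark in an arm of 30.** 11/30 = 36.7% fails and 12/30 = 40% passes.

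**3. Smallest joint adherence compatible with a pass.** Let P and E be the proportions meeting the protein and exercise targets. Then either = P + E − both, and both can lie anywhere from max(0, P + E − 1) to min(P, E).
- 12 protein-only participants: either 12/30, both 0/30, pass.
- 12 exercise-only participants: the same.
- 6 protein-only and 6 exercise-only: either 12/30, both 0/30, pass.

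So a pass guarantees nothing about joint adherence. With a denominator of 60 the pass mark would be 23/60 (38.3%) and the logic would not change.

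**4. Size under different overlap.** With the same rate p for each component and correlation phi:

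both = p² + phi × p(1 − p); either = 2p − both.

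Example, p = 0.40 and phi = 0.5: both = 0.16 + 0.5 × 0.24 = 0.28; either = 0.80 − 0.28 = 0.52. The last two columns give the binomial chance of at least 12 of 30.

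| Assumed p | Overlap | Either | Both | Pass, either | Pass, both |
|---|---|---|---|---|---|
| 40% | independent | 64% | 16% | 99.8% | 0.1% |
| 40% | phi = 0.5 | 52% | 28% | 93% | 11% |
| 40% | full | 40% | 40% | 57% | 57% |
| 50% | independent | 75% | 25% | > 99.9% | 5.1% |
| 50% | phi = 0.5 | 62.5% | 37.5% | > 99% | 46% |
| 30% | phi = 0.5 | 40.5% | 19.5% | 59% | 0.8% |
| 21% | phi = 0.5 | 29% | 13% | 14% | < 0.1% |

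The gap between the two definitions is wide at moderate overlap and disappears at full overlap. At low component rates with moderate overlap, the expected rate is below the bar even under the lenient rule.

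**The case against.** **Overlap is probably positive.** The article asks for protein within 3 h after exercise, the same physiotherapist calls support both parts, and one log covers both. Independence and zero overlap are therefore unfavourable cases. This stands, and it is why the size must be given as a range. It does not remove the point: at phi = 0.5 and 40% per component, the chance of passing is still 93% under one definition and 11% under the other.

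**The consequence is limited.** A reader might infer that the rule could by itself send an undelivered intervention to a full RCT. The article does not support that. Green also requires recruitment and retention to pass, and failing adherence alone leads to modification, not a stop. The harm is green in place of amber. The logs, the proforma on reasons for non-adherence, the acceptability questions and the interviews would also reveal poor uptake of one part, although none of them enters the formal rule.

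**A lenient rule can be legitimate.** In a pragmatic feasibility study, substantial engagement with either part might count. The rationale for combination is also worded cautiously, and the article nowhere says that one part alone is worthless. This stands as far as it goes, but the choice is not explained. Leniency is already built in through the days per week, the 10 of 12 weeks and the 37% bar.

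**The connector may mean separate assessment of each part.** The single adherence rate in the progression rule would then have no defined numerator, so the text would still need correcting.

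**Conclusion.** The point holds, as something that should be fixed. As written, the adherence element can be met at 12/30 (40%) with few or no participants doing both parts of a combined intervention. That conclusion is a matter of logic and needs no assumed rates; it rests only on the literal reading of the connector and an arm of about 30.

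The likely inflation cannot be fixed from the article. At an assumed 40% per component it runs from 48 percentage points if independent (64% against 16%), through 24 points at phi = 0.5 (52% against 28%), to none at full overlap. The zero-overlap case is what the rule permits, not what should be expected. The decision at risk is green instead of amber, and only if recruitment and retention also pass.

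**What to change.** - Base the adherence progression criterion on participants who meet both component definitions.
- Report four proportions with 95% intervals: protein, exercise, either and both.
- Confirm or restate the expected 50% and the 37% bar for the joint definition. Replacing the connector while leaving these figures untouched would pair a stricter definition with a bar not shown to fit it: with 50% adherence to each component and independence, joint adherence is 25% and the chance of reaching 12/30 is 5.1%.

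If the sponsor prefers to keep the either-component rule, the article should justify it and add a joint or per-component condition to the progression rule.

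No new data are needed, because the daily logs already record both components. The cost is a lower, less favourable adherence figure and a threshold that has to be justified again.

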#### Secondary feasibility outcomes

Completion rates for questionnaires administered at baseline and 12 weeks after randomisation will be calculated. We will estimate the efficacy potential of the intervention using the preoperative WOMAC score at 12 weeks after randomisation. The primary outcome for a future full RCT would be in the post-operative period to reflect that prehabilitation aims to optimise post-operative outcomes. While we are not collecting post-operative patient-reported outcomes in this feasibility study due to our study timelines, preoperative pain and function will give an indication of efficacy potential as they are the strongest predictors of post-operative function and pain after joint replacement [32, 33].

#### Progression criteria for a full-scale RCT

The key feasibility issues will be considered on a red (stop), amber (amend), and green (proceed) traffic light system. The feasibility of a full trial will be determined by overall recruitment, retention, and adherence rates. Recruitment will be considered achievable if the rate observed is > 23% (lower limit of the 95% confidence interval for a 30% recruitment rate based on 200 screened). Similar criteria will be applied for retention: i.e. > 70%, for an 80% retention rate based on 60 participants, for adherence: > 37%, and for a 50% adherence rate based on 60 participants. If all three elements fail to reach the threshold (i.e. recruitment is ≤ 23%, retention is ≤ 69%, and adherence is ≤ 37%), a RCT will not be considered feasible. If one or two elements fail to reach the threshold, we will consider how the trial can be modified to address the shortfall. Examples may include modifying recruitment processes or study documents (recruitment), providing additional support/advice (retention and adherence), or offering alternative protein-rich products/exercises (retention and adherence). If all three elements are above the threshold, the trial will be considered feasible.

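### Retention is judged only as one rate pooled over both arms, so that element can pass with half the intervention arm lost; an intervention-arm check would be a cheap improvement

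*Protocol article*

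**What the plan says.** All references are to the Protocol article.

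- **Progression criteria for a full-scale RCT** sets the level of judgement: "The feasibility of a full trial will be determined by overall recruitment, retention, and adherence rates". The retention bar is introduced by "Similar criteria will be applied for retention: i.e. > 70"%, and its basis is "for an 80% retention rate based on 60 participants". The rule for proceeding is: "If all three elements are above the threshold, the trial will be considered feasible". If one or two elements fall short, the team considers modifications. If all three fall short, an RCT is not considered feasible.
- **Primary feasibility outcomes** gives retention a second use: "Acceptability of the trial and intervention will be evaluated through qualitative interviews, questions in the study questionnaires, retention rates, and reasons for withdrawal". No split by arm or threshold is attached to that use.
- **Abstract, Methods** says the sixty participants "will be recruited and randomly allocated on a 1:1 ratio to the intervention or usual care group", so about 30 receive the intervention.

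No section sets a retention criterion for one arm or a limit on the difference between arms. Reasons for withdrawal and the interviews are collected, but the progression rule gives them no stated effect.

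**The concern.** The two arms ask different things of participants. The intervention arm has a daily protein supplement, a daily home exercise programme, an initial physiotherapy appointment and six calls. Usual care adds nothing to routine treatment beyond the study questionnaires. Allocation is known to participants. If the intervention is burdensome, loss could concentrate in that arm.

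The plan treats retention partly as a signal about the intervention. It is listed as a measure of acceptability, and the suggested remedies for poor retention include other protein products or exercises. The progression rule then averages that signal with an arm that never received the intervention. Unequal loss between arms threatens the validity of an unblinded definitive trial, and the retention element as written cannot register it.

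**Working it through.** **Inputs.** From the progression criteria: 80% anticipated retention, n = 60, bar above 70%; 50% anticipated adherence, printed n = 60, bar above 37%; 30% recruitment, n = 200, bar above 23%. From the Abstract: 60 participants, 1:1. Assumptions: exactly 30 per arm; retained means still in follow-up at 12 weeks; independent binomial losses.

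**1. Reproduce the plan's bars.** Lower limit = p − 1.96·√(p(1−p)/n).
- Retention: 0.80 − 1.96·√(0.16/60) = 0.80 − 0.101 = 0.699, stated as 70%.
- Adherence: 0.50 − 1.96·√(0.25/60) = 0.50 − 0.127 = 0.373, stated as 37%.
- Recruitment: 0.30 − 1.96·√(0.21/200) = 0.30 − 0.0635 = 0.2365, stated as 23%.

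With n = 30 the retention limit would be 0.80 − 1.96·√(0.16/30) = 0.657, so the printed bar is a pooled one.

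**2. Which splits pass.** Above 70% of 60 means at least 43 retained (43/60 = 71.7%). With 15/30 in the intervention arm:

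| Usual care retained | Pooled | Retention element |
|---|---|---|
| 30/30 | 45/60 = 75.0% | passes |
| 29/30 | 44/60 = 73.3% | passes |
| 28/30 | 43/60 = 71.7% | passes |
| 27/30 | 42/60 = 70.0% | does not exceed 70% |

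**3. How often the retention element passes.** P(U + I ≥ 43), with U ~ Bin(30, p_U) for usual care and I ~ Bin(30, p_I) for the intervention arm:

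| True retention (usual care / intervention) | P(retention passes) |
|---|---|
| 95% / 55% | 0.80 |
| 95% / 50% | 0.63 |
| 90% / 50% | 0.44 |
| 85% / 50% | 0.28 |

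**4. Adding the adherence element.** Assume a denominator of 30, so at least 12 adherers are needed (12/30 = 40%; 11/30 = 36.7% fails), and that nobody lost counts as adherent. With A ~ Bin(I, a), where a is adherence among those retained, P(U + I ≥ 43 and A ≥ 12) is:

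| a | 95% / 55% | 95% / 50% |
|---|---|---|
| 50% | 0.09 | 0.05 |
| 62.5% (the plan's 50% ÷ 80%) | 0.31 | 0.19 |
| 80% | 0.67 | 0.49 |

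If the printed basis, "for a 50% adherence rate based on 60 participants", is taken as the denominator, at least 23 adherers are needed (23/60 = 38.3%). Fifteen retained participants give at most 15/60 = 25%, so adherence fails and the overall result is amber.

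**5. Effect of an intervention-arm bar at 65.7%.** The smallest passing count is 20/30 = 66.7%. P(U + I ≥ 43 and I ≥ 20):
- 95% / 55%: 0.80 falls to 0.14.
- 95% / 50%: 0.63 falls to 0.05.
- 80% / 80%: 0.957 falls to 0.944.

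Chance of missing the added bar at true intervention-arm retention of 80%: P(Bin(30, 0.8) ≤ 19) = 0.026.

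**The case against.** A pooled retention criterion in a 60-person feasibility study is neither a contradiction nor an arithmetic error. The case against making much of it has several parts.

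- **The 80% and 63% are not chances of a feasible verdict.** A reader might infer that they are. The documents do not support that: all three elements must pass, and adherence can be met only by people receiving the intervention. Loss in that arm lowers the possible number of adherers, so adherence is a partial arm-specific check. This stands, and step 4 shows how much lower the joint chances are.
- **A reader might infer that one-sided loss could never produce an amber result.** That is also unsupported. With the printed denominator of 60, fifteen retained participants cannot pass adherence. That denominator is itself doubtful, because only about 30 people can adhere, so it is not a designed safeguard. The resulting amber would also point to adherence, while the retention element still passed.
- **The passing cases need high usual-care retention.** With 15/30 in the intervention arm, usual care must keep at least 28/30. This stands. At 85% / 50% the element passes 28% of the time.
- **One-sided loss is not documented.** The article gives no expected retention by arm, and participants who know they are in usual care may also leave. This stands; the unequal burden makes one-sided loss plausible and no more.
- **Differential loss would be seen elsewhere.** Interviews, questionnaire items and withdrawal reasons would probably reveal it. True, but none of these has a stated effect on the progression decision.
- **Reporting retention by arm may sit in the SAP.** Accepted; its absence from the article is not a fault. The point concerns the decision rule, which the article does fix.

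**Conclusion.** The point holds for the retention element. It is judged only on a pooled rate, and the 70% bar reproduces only with both arms combined. It can therefore pass with 15/30 retained in the intervention arm when usual care retains 28/30 or more. At true retention of 95% / 55% and 95% / 50% it passes about 80% and 63% of the time.

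The chance that retention and adherence both pass is lower: about 31% and 19% if 62.5% of those retained adhere, with a range from 9% and 5% (half adhere) to 67% and 49% (80% adhere). An overall feasible verdict also needs recruitment to pass. These figures rest on 30 per arm, an adherence denominator of 30, no adherence among those lost, and assumed true retention rates, since the article gives none by arm. This is a worthwhile improvement to the rule, not a flaw that invalidates it.

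**What to change.** Keep the pooled bar and add one sentence to Progression criteria for a full-scale RCT: the retention element is amber unless intervention-arm retention also exceeds 65.7% (at least 20 of 30), the lower 95% limit for 80% retention with n = 30. If the arms are not exactly 30, recalculate the limit by the same formula.

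The cost is one sentence and a small risk of an unnecessary amber. If true intervention-arm retention is 80%, the added bar is missed 2.6% of the time. Some of those cases already fail the pooled bar, so when both arms truly retain 80% the retention pass rate falls only from 95.7% to 94.4%. The risk is larger if true retention is below 80%: at an assumed 75%, P(Bin(30, 0.75) ≤ 19) = 0.106. A miss leads to a review of how the trial could be modified, not to a stop.
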